##### Grading of dermatologic toxicity

NCI CTCAE is commonly used to monitor and rate the severity of chemotherapy-induced toxicity [27]. The CTCAE displays grades 1 through 5 with unique clinical descriptions of severity for each adverse event. Protocol-defined dermatologic toxicities include dry skin, pruritus, skin ulceration, acneiform rash, maculopapular rash, skin pain, skin hyperpigmentation, palmar-plantar erythrodysesthesia syndrome, scalp pain, alopecia, paronychia, nail discoloration, nail ridging, and nail loss, which are elaborated in Additional file 1. To reduce bias, the symptoms will be recorded according to therapist diagnosis and patient reports, but will not be graded in the presence of the patients.

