**Methods/design:**

This is a prospective assessor-blinded, parallel, randomized controlled trial. Patients with cancer at any stage who have completed chemotherapy within two weeks will be randomly divided into group A (YH0618) and group B (wait-list) using a 1:1 allocation ratio. The chemotherapeutic agents include taxanes or anthracyclines. Subjects assigned to group A will receive YH0618 soup 6 days a week for 6 weeks and uncontrolled follow-up for 6 weeks, while group B are required to wait for 6 weeks before receiving YH0618 intervention. The primary outcome of this study is the incidence of protocol-specified grade ≥2 dermatologic toxicities graded by NCI CTCAE Chinese version 4.0 and changes of fingernail color, face skin color and tongue color evaluated by the L*a*b system within 6 weeks. There are some secondary outcomes associated with dermatologic toxicity including fatigue and clinical objective examination.

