### Randomization and blinding

The research assistant will give each patient a unique study number immediately after they complete the written consent. A computer random digit (randomization list) will be generated by a statistician not involved in this study. Codes representing the two groups will be printed on one A4 opaque paper, and then be put into a envelope which is blotted out using double sided tape. The tape should be torn by the patients themselves just after completing the baseline testing. Because this trial compares the effects of the YH0618 group and the wait-list group, it is not possible to blind the patients; thus, they know which group they are in. However, the randomization sequence and different groups will be kept hidden from the practitioners, data collectors, and statisticians.

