### Outcome evaluation

#### Primary outcome

The primary outcome of this study is the incidence of specific grade ≥2 dermatologic toxicities and changes of nail color, skin color, and tongue color after 6 weeks of intervention which will be graded by NCI CTCAE Chinese version 4.0 and evaluated by the L*a*b system, respectively.

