*Nephrotoxicity:* Liver and kidney function are important indicators in evaluating drug safety. Moreover, based on the theory of homogeny of liver and kidney in Chinese medicine, it is necessary to test kidney function. In the testing of kidney function, injury to the kidney can be exactly reflected by creatinine in the blood. The concentration change of creatinine is determined by the glomerular filtration rate, and only at a rate down to one-third of normal will the creatinine increase significantly [35]. In addition, blood urea nitrogen (BUN) is an important indication of renal (kidney) health. Therefore, creatinine (Cr) and BUN will be used as indexes to assess nephrotoxicity.

All participants will be assessed before the intervention (baseline), and 3, 6, and 12 weeks after intervention. All YH0618 materials conform to Food and Environmental Hygiene Department’s requirement for food safety and achieve the certificate of quality. The packing will be conducted at clinics of the School of Chinese Medicine, HKU. A professional research assistant will teach the subjects how to decoct the YH0618 soup, and the specific intake, water amount, and decoction time will be provided to each subject. These subjects will be asked to complete the questionnaires, undergo blood tests by themselves in hospitals, and send all testing results. Quality and compliance to intervention will be achieved by checking attendance records and the diary of self-record kept by each participant. All outcome assessors will be blinded to the intervention types of participants.

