## Discussion

This is the first strict randomized controlled trial to evaluate the effect of medical food on ameliorating chemotherapy-induced toxicity. The proposed study may provide direct and convincing evidence to support YH0618 as an adjuvant treatment for reducing chemotherapy-induced toxicity, which could be introduced into clinical settings. Since little attention has been given to exploring the role of medical food intervention in reducing chemotherapy-induced toxicity, this study will provide solid scientific evidence for international healthcare policy makers to support the integration of alternative intervention strategies in providing care to patients with cancer. When considering that more and more cancer patients are facing chemotherapy-induced side effects even after they have completed chemotherapy, our achievements will provide a safe and effective way for reducing chemotherapy-induced toxicity and improving their quality of life. The objective assessments for chemotherapy-induced toxicity, such as color index, are another important advantage in this study.

However, the main potential limitation of this protocol is that it is not double-blinded. A placebo would not be used in this study, because it is difficult to make a dietary placebo with the limited manpower and finances at this stage. It is also more fair to the wait-list group, as all of the subjects have opportunities to drink the YH0618 soup. If the results are positive, we will further compare the differences of the YH0618 soup and a placebo in order to avoid psychological effects in the future. Although the participants are not blinded, all of the evaluators and statisticians are blinded.

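### The grade ≥2 dermatologic toxicity outcome that sizes the trial draws on reports from unblinded patients, and blinding the assessor does not protect those reports

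*Protocol article*

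**What the plan says.** The abstract labels the design: "This is a prospective assessor-blinded, parallel, randomized controlled trial". The section Randomization and blinding states that "it is not possible to blind the patients; thus, they know which group they are in". The Discussion adds that no placebo is used.

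The Primary outcome section names "the incidence of specific grade ≥2 dermatologic toxicities and changes of nail color, skin color, and tongue color after 6 weeks of intervention". Estimation of sample size uses only the first of these, the proportion of subjects with grade ≥2 toxicity.

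Grading of dermatologic toxicity lists 14 items: "dry skin, pruritus, skin ulceration, acneiform rash, maculopapular rash, skin pain, skin hyperpigmentation, palmar-plantar erythrodysesthesia syndrome, scalp pain, alopecia, paronychia", followed by nail discoloration, nail ridging and nail loss. On the data source and the safeguard it says that "the symptoms will be recorded according to therapist diagnosis and patient reports, but will not be graded in the presence of the patients". The stated aim of this step is to reduce bias.

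At the end of the outcome sections the article says: "All outcome assessors will be blinded to the intervention types of participants". The Discussion concedes that "the main potential limitation of this protocol is that it is not double-blinded", mentions psychological effects as a matter for a later placebo comparison, and offers the blinding of evaluators and statisticians in reply. It does not say there that a primary outcome takes input from the patients themselves.

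**The concern.** Assessor blinding protects an outcome to the extent that the assessor generates the data. Here part of the data comes from the patient, who knows whether he or she is drinking the soup or waiting for it. Someone on the wait-list may report more itch or pain, and someone on the soup may report less, with no difference in the skin. A blinded grader who works from such a report produces a grade that carries the same shift. Keeping the patient out of the room while the grade is assigned prevents influence on the grader at that moment but does not change what was recorded beforehand.

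The endpoint is the proportion of subjects with grade ≥2, so a single sensation graded 2 or higher can turn a patient into an event. At stake is how a positive result on this outcome may be read. It could reflect less toxicity, a difference in reporting, or both, and the label assessor-blinded would lead readers to discount the second.

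**Working it through.** **1. The plan's own figure.** Inputs from Estimation of sample size: 30% control, 10% soup, alpha 0.05, power 90%, Z-test for two proportions. With pooled variance under the null, two-sided and without continuity correction:

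n = [1.960·√(2·0.20·0.80) + 1.282·√(0.30·0.70 + 0.10·0.90)]² / 0.20²
= [1.960·0.5657 + 1.282·0.5477]² / 0.04
= 1.8107² / 0.04 = 81.96, so 82 per group.

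Attrition: 82 / (1 − 0.30) = 117.1, so 118 per group and 236 in total. Both figures reproduce and are not in dispute.

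**2. Which parts of the primary outcome depend on the patient's word.**

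| Component | Source in the article | Depends on patient report? |
|---|---|---|
| Grade ≥2: pruritus, skin pain, scalp pain | therapist diagnosis and patient reports | Yes; the sensation cannot be observed by an examiner |
| Grade ≥2: the other 11 items | the same sentence | Possibly; signs such as ulceration or nail loss can be checked by examination |
| L\*a\*b colour | digital photographs with fixed set-up and calibration chart | No |

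**3. What a reporting gap would do.** The documents give no figure for reporting bias, so the gap b is an assumption, shown over a range. Suppose no true effect and a rate of 30% in both arms (the article's control rate), with the apparent soup-arm rate lowered to 0.30 − b. The same two-sided pooled Z-test then rejects with probability

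P = 1 − Φ[(1.960·s₀ − b)/s₁] + Φ[(−1.960·s₀ − b)/s₁],

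where s₀ = √(2·p̄(1 − p̄)/n), p̄ is the mean of the two apparent rates, and s₁ = √{[p₁(1 − p₁) + p₂(1 − p₂)]/n}.

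Example with b = 0.10 and n = 82: p̄ = 0.25, s₀ = 0.0676, s₁ = 0.0672. Then (1.960·0.0676 − 0.10)/0.0672 = 0.48, giving an upper-tail probability of 0.314; the other tail adds less than 0.001.

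| Between-arm gap b | 82 per arm | 118 per arm |
|---|---|---|
| 0 | 5% | 5% |
| 3 points | 7% | 8% |
| 5 points | 11% | 14% |
| 10 points | 31% | 43% |
| 15 points | 64% | 79% |

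A larger sample makes the problem worse, because it estimates the biased difference more precisely.

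**4. What limits b.** A patient with a grade ≥2 sign that the examiner can see is an event whatever he or she reports. Only patients whose status depends on their own report can move, and the article does not say how many there are. The larger gaps in the table are therefore not predictions.

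**The case against.** The strongest reply is that the trial does not rest on patient report alone. Colour change is also a primary outcome, is measured from calibrated photographs, and is compared at 6 weeks by t test for nail and skin colour; blood, liver and renal markers are secondary outcomes. This stands. A reader might infer that the trial has no outcome protected from expectation, and the documents do not support that. But colour says nothing about pain, itch, ulceration or rash, so it cannot verify the grade ≥2 comparison.

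Second, the article is open about the design: it claims only to reduce bias and names the lack of double-blinding as its main limitation. That softens the point. It does not remove it, because the answer offered is the blinding of evaluators, which does not reach the patient's report.

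Third, a reader might infer that assessors are in fact unblinded, since the soup is packed at the clinics where outcomes are assessed and compliance is judged by "checking attendance records and the diary of self-record kept by each participant". The documents do not say that assessors handle the diaries or the soup. They give decoction teaching to a research assistant and say that allocation is hidden from practitioners and data collectors. How tasks are divided in detail is commonly left to a fuller document, so no finding is made on it.

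Fourth, the item definitions are in Additional file 1, which is not shown, and the article names therapist diagnosis as a source alongside patient reports. It therefore cannot be said that any item rests on patient report alone, only that a sensation cannot be confirmed by inspection.

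**Conclusion.** The point holds for the CTCAE grade ≥2 outcome. Its data come partly from patients who know their arm, its items include three sensations, and the one safeguard stated for the grading protects the grader and not the report. For this outcome the description assessor-blinded claims more protection than the procedure gives.

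The size of the bias cannot be derived from the documents. The figures of about 7%, 11% and 31% at 82 per arm (8%, 14% and 43% at 118) rest on assumed between-arm gaps of 3, 5 and 10 points, a 30% rate in both arms and no true effect. They show how sensitive the test is to such gaps, not that such gaps will occur. The colour outcome and the sample size calculation are unaffected. This is an inexpensive improvement that limits what a positive grade ≥2 result may claim; it does not invalidate the trial.

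**What to change.** Pre-specify a supportive analysis of grade ≥2 incidence at 6 weeks that excludes pruritus, skin pain and scalp pain and counts the remaining items only where the blinded assessor's examination confirms the sign. Dropping the three sensations is not enough by itself, because the sentence on patient reports covers all 14 items. Report the relative risk and 95% CI of this analysis beside the primary result.

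Describe the grade ≥2 outcome as partly patient-reported and not fully assessor-blinded. Call the effect robust to reporting bias only if the signs-only estimate is of similar size. Agreement in direction alone is too weak a standard: with no true effect, an independent comparison would favour the soup about half the time.

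The cost is one extra analysis of grades already collected, provided that examination findings are recorded separately from patient reports. The downside is fewer events and a wider interval, and the supportive analysis leaves out symptoms that matter to patients. For that reason it should stand beside the primary analysis and not replace it.

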##### Skin, nail, and tongue color measurement

In order to evaluate the changes of skin, nail, and tongue color objectively, L*a*b will be used. The L*a*b system, determined by the International Commission on Illumination (CIE) in 1976, is a “gold standard” in assessing color. In the CIELAB color space, values L*, a*, and b* form a three-dimensional coordinate system by plotting at right angles to one another [28]. Value L* represents light/dark and extends from 0 (black) to 100 (white). Value a* represents the red/green axis, and value b* represents the yellow/blue axis. Recently, many methods are available to measure skin color, such as visual assessment, rating scales, photography, reflectance spectroscopy, etc. After analyzing the advantages and disadvantages of the methods, we decided to adopt digital images in this study. Digital image analysis has been used for more than 15 years in medical imaging; it does not directly contact the skin and therefore cannot disturb the measurement of skin color (e.g., by blanching the skin). The digital camera and environment like lighting source and position, background, and distance between camera and subject will be fixed. First, we will use a Canon® digital camera to take pictures. In order to reduce interference from the external environment, a calibration color chart (Spyder CHECKR 24) will be adopted. Then, the Color Sampler tools in Adobe PhotoShop Creative Suite 6 (CS6) will be used for digital image color analysis, which can retrieve and record L*a*b* color values. We will record the skin color of the forehead, right and left cheeks, jaw, and dorsum of the right and left hands, the nail color of ten fingernails, and tongue color.

#### Secondary outcomes

##### Fatigue measurement

Fatigue is an obvious symptom in patients with cancer who are receiving chemotherapy. Fatigue will be measured by the Chinese version of Functional Assessment of Chronic Illness Therapy-Fatigue version 4 (FACIT-F), which can be used with any tumor type [29]. It consists of 40 items scored on a 5-point Likert scale, ranging from 0 to 4. It has five subscales including Physical Well-Being, Social/Family Well-Being, Emotional Well-Being, Functional Well-Being, and Additional Concerns. A total score will be obtained by summing all subscale scores.

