## Methods/design

### Study design

This is a randomized controlled trial which aims at determining whether YH0618 would be more effective than the wait-list control conditions in ameliorating chemotherapy-induced dermatologic toxicity, blood system disorders, and hepatic and renal disorders and in improving fatigue in cancer patients who have completed chemotherapy. To achieve this goal, a total of 236 patients with cancer at any stage who have completed chemotherapy within 2 weeks will be recruited for the study. The patients will be randomly divided into group A (YH0618) and group B (wait-list) using a 1:1 allocation ratio, adhering to the Consolidated Standards of Reporting Trials (CONSORT) statement [25] and the Standard Protocol Items: Recommendations for Interventional Trials (SPIRIT) statement [26]. The measures of clinical outcomes mainly include the grading of dermatologic toxicity, skin color, nail color, tongue color, and score of fatigue. Several biomarkers associated with myelosuppression, hepatotoxicity, and nephrotoxicity in the blood will also be measured. The flow chart of the study is shown in Fig. 1, and the trial process is listed in Table 1. The evaluation and data collected will be conducted at the clinics of the School of Chinese Medicine, HKU.

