**Fig. 1 Fig1:**
[figure not shown]
Flow chart of the clinical trial

**Table 1 Tab1:** Trial process chart

	Before baseline screening	Baseline	Visit 1 Treatment phase	Visit 2 Treatment phase	Visit 3 Follow-up phase
Process items		0 day	3 weeks	6 weeks	12 weeks
Patients					
Inclusion and exclusion criteria	×				
Informed consent		×			
Demographics		×			
Medical history	×	×			
Randomization and allocation concealment		×			
Primary outcomes					
Grading of dermatologic toxicity		×	×	×	×
Objective skin, nail, and tongue color (L*a*b)		×	×	×	×
Secondary outcomes					
Fatigue measurement score		×	×	×	×
Routine blood test (WBC, HGB, PLT)		×	×	×	×
Liver function (ALT, AST, total protein, Alba)		×	×	×	×
Renal function (Cr and BUN)		×	×	×	×
Adverse events			×	×	×
Patients’ diary records		Every day during the study			

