### Statistical analysis

Statistical analysis will be conducted by a statistician using SPSS version 22.0. Analyses will be performed based on intention-to-treat principles, and any missing data in the follow up visits will be imputed using multiple imputation.

Descriptive statistics will be used to summarize the baseline demographics and clinical characteristics for both groups. Missing values at follow-up visits or drop-outs in the two groups will be assessed to identify any potential bias.

For the primary outcomes, relative risk for the incidence of dermatologic toxicities with grade ≥2, including 95 % CIs obtained via normal approximation to the binomial distribution, will be analyzed for the two groups. The changes in nail color and skin color from baseline to 6 weeks will be compared between the two groups by independent sample *t* tests. Because participants will be randomized into the intervention group or wait-list group, little confounding is expected. However, potential confounding variables will be identified as those that differ among treatment groups at baseline and are significantly associated with outcomes. In case any potential confounders are identified, a logistic regression model and a multiple linear regression model will be used to analyze the binary and continuous outcomes, respectively.

In further analyses using measures at all time points, the relative effectiveness of the interventions, including all primary and secondary outcomes, will be assessed in repeated measures mixed models, using the generalized estimating equation (GEE) modeling method. The repeated measures regression models account for the correlations between individual measurements when repeated over time. The primary test of effect depends upon differing patterns of change (slope) over time; thus, differences in slope will be identified by significant interactions of intervention group with time. If the interaction terms are significant, then further analyses will use contrasts within the models to compare groups at each time point and to compare outcomes across time within each group.

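### The only score defined for the fatigue outcome is a five-domain FACIT-F total, which does not isolate fatigue

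*Protocol article*

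**What the plan says.** The Study design section of the protocol article includes among the trial's aims an effect "in improving fatigue in cancer patients who have completed chemotherapy". The same section names the measure among the main clinical outcomes: "skin color, nail color, tongue color, and score of fatigue". Table 1 lists it under secondary outcomes as "Fatigue measurement score", collected at baseline and at 3, 6 and 12 weeks.

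The Fatigue measurement section gives the instrument, the FACIT-F version 4 in Chinese, and describes it: "It consists of 40 items scored on a 5-point Likert scale, ranging from 0 to 4". On structure it says: "It has five subscales including Physical Well-Being, Social/Family Well-Being, Emotional Well-Being, Functional Well-Being, and Additional Concerns". On scoring it says only: "A total score will be obtained by summing all subscale scores".

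The Statistical analysis section names no FACIT-F score. It covers the outcome through a general statement that the analyses, "including all primary and secondary outcomes, will be assessed in repeated measures mixed models", use GEE. No quality-of-life outcome is listed in the article.

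**The concern.** The label and the defined quantity do not match. The aim is about fatigue, and the Background gives fatigue a physiological role as a reflection of liver and kidney toxicity. The scoring rule adds social/family and emotional well-being, which have no part in that argument, to whatever measures fatigue.

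Two errors of interpretation become possible:

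- A difference between arms that arises in the social or emotional domains would be read as a benefit on fatigue.
- A real benefit confined to fatigue would be spread over a total in which most of the named domains are something else, and could be missed.

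The article speaks of quality of life as a concept of its own in the Background and the Discussion, yet lists no outcome for it. A total of this kind would fit that concept better than the label it carries.

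**Working it through.** **1. The plan's own figures.** No effect size or power is stated for fatigue. The sample size is for the binary dermatologic outcome, and it reproduces. With 30% against 10%, two-sided alpha 0.05, 90% power and pooled variance under the null:

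n = [1.96·√(2·0.20·0.80) + 1.2816·√(0.30·0.70 + 0.10·0.90)]² / 0.20² = (1.109 + 0.702)² / 0.04 ≈ 82 per group.

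Allowing for 30% attrition, 82/0.70 = 117.1, so 118 per group and 236 in total. Nothing below alters these figures.

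**2. What the defined score contains.** With 40 items scored 0 to 4, the total runs from 0 to 40 × 4 = 160. Four of its five components are well-being domains by their own names. The article does not say which subscale carries the fatigue items or how many items each has. That Additional Concerns is the fatigue part follows only by elimination.

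**3. Label against definition.** The Study design section and Table 1 attach the word fatigue to one score. The Fatigue measurement section defines one score, the sum of all five subscales. No section names a subscale for separate analysis. Read together, the score called fatigue is the five-domain total.

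**4. Why the size cannot be fixed.** The following is an illustration; none of its inputs comes from the article. Let the fatigue subscale have k of the 40 items, with a = k/40 and b = 1 − a. Let each part's SD be proportional to its number of items, and let ρ be the correlation between the fatigue part and the rest. If the standardised effects on the two parts are dF and dW, the standardised effect on the total is

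d(total) = (a·dF + b·dW) / √(a² + b² + 2ρab).

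Take k = 13, so a = 0.325 and b = 0.675. The denominator is √0.693 = 0.832 at ρ = 0.3 and √0.868 = 0.932 at ρ = 0.7.

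| Assumed effects | d(total), ρ = 0.3 | d(total), ρ = 0.7 |
|---|---|---|
| Fatigue only: dF = 0.5, dW = 0 | 0.1625/0.832 = 0.20 | 0.1625/0.932 = 0.17 |
| Well-being only: dF = 0, dW = 0.5 | 0.3375/0.832 = 0.41 | 0.3375/0.932 = 0.36 |
| Both: dF = dW = 0.5 | 0.5/0.832 = 0.60 | 0.5/0.932 = 0.54 |

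The first row is dilution. The second is a change in the fatigue score with no change in fatigue. The third shows that the total loses nothing if all domains improve alike.

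For the first row, a simple two-group comparison with 82 per arm has power Φ(d·√(82/2) − 1.96). That is Φ(1.24) = 89% for the subscale and 20% to 24% for the total. If k ranges from 8 to 16, d(total) is 0.11 to 0.25 and power is 10% to 35%. The 82 per arm is borrowed from another endpoint, and the planned GEE uses all visits, so these percentages do not describe this trial.

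**The case against.** The strongest case against is that this is a condensed article with no analysis plan shown. It says that a total will be obtained, not that only the total will be analysed, and a total formed from subscale scores presupposes that each subscale is scored. A fuller document could name the subscale. This stands as a limit: the article does not show that the trial will report nothing but the total. It does not dispose of the point, because the article is not silent. It states a scoring rule under the fatigue heading, and that rule does not match the aim.

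Four stronger readings are tempting, and the article does not support them:

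- **That fatigue is the leading secondary outcome.** Table 1 lists it with blood, liver and renal measures and gives no ranking.
- **That a definite amount of power is lost.** One could assume an effect of 0.4 SD on fatigue alone, uncorrelated parts and a one-third share of the variance. Then 0.4·√(1/3) = 0.23, and power at 82 per arm falls from about 73% to about 31%. The arithmetic is right, but every input is assumed, and the loss shrinks or vanishes if physical and functional well-being also improve.
- **That the total is what lets wait-list disappointment into the result.** Patients are unblinded, and any self-reported score, a fatigue subscale included, is exposed to this. The total adds a mood domain by construction, but removing it does not cure the bias.
- **That the article identifies Additional Concerns as the fatigue subscale.** It gives only the name, so the instrument must be checked.

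**Conclusion.** The point holds as a mismatch between a stated aim and a stated scoring rule. As written, the fatigue score is the sum of five domains, four of them named as well-being, so it cannot separate a change in fatigue from a change in social, emotional, physical or functional well-being. This rests on the article's own subscale names and on the absence of any other defined score; it needs no assumption about item counts. The size of the dilution is unknown. The illustrations show only that the total could understate, overstate or preserve an effect, depending on which domains move.

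The consequence is limited to one secondary outcome. It is worth correcting because it changes what the trial can conclude about fatigue, and because leaving the choice between total and subscale open until data are seen would invite selective reporting.

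**What to change.** In the Fatigue measurement section, name the fatigue-specific FACIT-F subscale as the fatigue outcome, after confirming against the instrument that this is Additional Concerns. Analyse it as the Statistical analysis section already plans for secondary outcomes, over all visits; nothing here calls for restricting it to one time point. Report the 40-item total and the four well-being subscales separately, labelled as quality-of-life outcomes. Table 1 and the Study design section should then refer to the subscale wherever they mention the fatigue score.

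The cost is a sentence or two of text and one more score to report. The questionnaire, the visits and the sample size stay as they are.
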